### Statistical analyses

2.11

The disability level will be the principal outcome, measured by WHODAS-12 (primary outcomes), and upper limp Fugl-Meyer (secondary outcome). The global cognitive status, assessed by MoCA, will be also a primary outcome. According to the data distribution, parametric or nonparametric statistical tests will be used. In particular, the independent Student *t* test or the Mann–Whitney *U* test will be used to compare the 2 groups, whereas the Student *t* test for unpaired samples or the Wilcoxon signed-rank test will be used to compare the data collected at the first evaluation and the end of the treatment (intragroup analysis). Linear correlation between variables will be computed by Pearson's coefficient or nonparametric Spearman's rank correlation coefficient. Statistical significance will be set at bilateral alpha level of 0.05. HTA assessment: Data will be collected by means of structured checklists, harmonized with all the units, to be administered to all involved actors. Any required data pooling, transformation, averaging, statistics and overall data processing will be performed by Unit 1 and 3 for assessing proper HTA indicators. With respect to cost analysis, specific direct, and indirect costs will be retrieved from each experimental study to allow performing Cost-Effectiveness and Cost-Minimization analysis within HTA3, to be possibly compared with corresponding cost analysis within HTA1. TR will be supported by the adoption of advanced ICT systems, necessary to set up videoconferencing between remote therapists and patient at home, monitor patient health status and activities, and store and process data collected during TR sessions. Monitoring systems will be composed by low-cost nonintrusive devices (such as bracelet or others).

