### Eligibility criteria

2.2

In both the clinical Units, we plan to enroll a total 40 stroke patients (20 for each treatment setting) and 40 TBI patients (20 for each condition) requiring home motor and cognitive rehabilitation.

Inclusion criteria are: age range 18 to 65 years; diagnosis of stroke and TBI (less than 1 year), according to neuroradiological and clinical assessments; availability of a home internet connection; the presence of a Montreal Cognitive assessment ≥16/30; the presence of a skilled caregiver.

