### Study population

2.6

All the patients will be divided into 2 groups, performing TR (G1) or standard rehabilitation training (G2). TR will be delivered by means of an advanced video-conferencing system, whereas the patient will be provided with low-cost monitoring devices, able to collect data about his/her health status and quality of life (QoL). In both the groups each treatment (either cognitive or motor, or both as per patient functional status) will last about 1 hour a day, 5 days/week, for 12 weeks. Clinical evaluations will be administered blindly, before and after the treatments. Besides the clinical scales, evaluation regarding burden of care and HTA will be administered by Unit 1 and 3 to contribute to study aims. Besides the analysis of patient and caregiver burden, we will perform an observational study to analyze the patient's suitability to cope with a new system of rehabilitative treatment delivery. Two structured telephone interviews will be administered to the patients (when possible) and/or their caregivers, and to all the healthcare professionals involved in the patient management, 1 week after the beginning and at the end of the TR.

Satisfaction with the program and occurrence of any problem or barrier will be assessed. Longitudinal evaluation will compare baseline scores reported at the first interview with the posttreatment scores.

Besides the general HTA assessment, a second observational study will be specifically focused on Local Health Units (LHU) to verify whether and to what extent the different organizational settings in 2 diverse Italian regions (i.e., Sicily and Veneto) may influence TR feasibility and costs. Initial investments for ICT solutions necessary for TR (videoconferencing system, monitoring equipment, Cloud-based storage and processing solutions) and direct healthcare cost associated with stroke and TBI survivorship will be assessed. One-year direct cost of stroke will be estimated using hospital and LHU electronic records and interview responses of poststroke patients/caregivers. Costs will be reported for 1 year poststroke, and modeled over the lifetime poststroke.

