### Sample size

2.10

Based on the pilot samples during study, we calculated a minimal sample size of 60 participants per group in this study, given a power of >80% to detect an interaction in the 2-way repeated measures, an effect size of 0.61, 4 variables, and 2 repeated measurements.

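### Power is stated for a repeated-measures interaction, but the analysis section names a two-group test on an unstated variable, without the pathology balancing factor

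*Protocol article*

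**What the plan says.** Section 2.10 (Sample size) gives a "minimal sample size of 60 participants per group", "given a power of >80% to detect an interaction in the 2-way repeated measures", with "an effect size of 0.61, 4 variables, and 2 repeated measurements". The two factors are not named; with two arms and two measurements, group by time is the evident reading. The scale of 0.61 is not given.

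Section 2.11 (Statistical analyses) makes WHODAS-12 and MoCA primary outcomes. Between groups, the independent Student t test or the Mann-Whitney U "test will be used to compare the 2 groups". Comparisons of the first with the last assessment are described separately, as intragroup analyses. No interaction, repeated-measures model or covariate is named. "Statistical significance will be set at bilateral alpha level of 0.05".

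Section 2.6 (Study population) states: "Clinical evaluations will be administered blindly, before and after the treatments". Section 2.5 (Randomization of participants) says patients are balanced for pathology and otherwise describes the scheme as simple. Section 2.2 (Eligibility criteria) plans 40 stroke and 40 TBI patients, 20 of each per arm. Two centres take part (section 2.1); centre is not named as a randomisation factor.

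**The concern.** Two adjacent sections name different analyses. A power statement holds only for the test that will be run on the effect-size scale that was assumed, and here neither can be matched to the named test. Section 2.11 also leaves the variable of the two-group test open for both primary outcomes. End score and change are different tests with different power, and the choice could be made after the data are seen.

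With 80 patients, precision matters. Baseline scores are collected before treatment and pathology is known at allocation, yet neither is named for the between-group comparison. The trial also aims to show non-inferiority (section 2.1), which calls for a between-group estimate with an interval. The within-group tests cannot supply that.

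**Working it through.** **Inputs.** From section 2.10: effect size 0.61, power above 80%, two measurements, 60 per group. From section 2.2: 20 + 20 = 40 per arm. From section 2.11: two-sided alpha 0.05. Assumed, because the document gives none: a pre-post correlation ρ of 0.5 to 0.7 (0.3 to 0.9 as a wider range), equal SDs at both times and no dropout. The one or two degrees of freedom spent on covariates are ignored, and the power figures take no credit for pathology. They are per outcome.

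**Step 1: the plan's own figure.** For two means, n per group = 2(z₀.₉₇₅ + z₀.₈₀)²/d² = 2(1.960 + 0.842)²/0.61² ≈ 42.2, so 43 (44 by exact t). For 90% power it is 57 (58). Formulas for the repeated-measures interaction, with 0.61 or 0.305 as Cohen's f, two or four groups and ρ of 0, 0.5 or 0.7, give total sizes of 6 to 63, never 120. The only variant tried that gives 60 is a two-group comparison at 0.05/4 = 0.0125 (62 by exact t), a split that the protocol does not state. The 60 was therefore not reproduced from any interaction formula tried.

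**Step 2: when the two sections agree.** With two arms and two times, the interaction contrast is the difference between arms in mean change. Its F equals the squared t statistic on change scores. In a numerical example both are 3.2046, while the squared t on end scores alone is 0.479. The sections therefore agree for the parametric test if change is meant, and disagree if end scores are meant.

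**Step 3: variance of the arm difference.**
- ANCOVA against end scores: 1 − ρ² = 0.75 at ρ = 0.5 and 0.51 at ρ = 0.7.
- ANCOVA against change: (1 − ρ²)/[2(1 − ρ)] = (1 + ρ)/2 = 0.75 and 0.85.

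**Step 4: power at 40 per arm.** Noncentral t with 2n − 2 degrees of freedom and noncentrality d√(n/2); for d = 0.61 this is 0.61 × √20 = 2.73. If 0.61 is in final-score SDs, d is 0.61 for end scores, 0.61/√[2(1 − ρ)] for change and 0.61/√(1 − ρ²) for ANCOVA. If it is in change-score SDs, d is 0.61 for change, 0.61√[2(1 − ρ)] for end scores, and the end-score d divided by √(1 − ρ²) for ANCOVA.

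| 0.61 in units of | ρ | End-score t | Change-score t | ANCOVA |
|---|---|---|---|---|
| final-score SD | 0.3 | 76.9% | 62.4% | 80.6% |
| final-score SD | 0.5 | 76.9% | 76.9% | 87.5% |
| final-score SD | 0.7 | 76.9% | 93.6% | 96.5% |
| change-score SD | 0.3 | 89.0% | 76.9% | 91.6% |
| change-score SD | 0.5 | 76.9% | 76.9% | 87.5% |
| change-score SD | 0.7 | 55.1% | 76.9% | 83.2% |
| change-score SD | 0.9 | 22.6% | 76.9% | 78.9% |

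ANCOVA is highest in every row. At 60 per group the simple test with d = 0.61 already has 91.2%, and ANCOVA at ρ = 0.5 to 0.7 has 96.9% to 99.6% (final-score SDs) or 96.9% to 94.9% (change-score SDs).

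**Step 5: pathology.** With 20 per arm in each pathology, a pathology difference of β within-group SDs cancels from the arm difference but stays in the unadjusted test's variance estimate, adding about β²/4 (1.25 instead of 1 at β = 1). In 20,000 simulated trials the type I error was 5.25% at β = 0, then 4.5%, 3.0% and 1.4% at β = 0.5, 1.0 and 1.5. The test becomes conservative. This assumes that the balance is enforced, as section 2.2's counts imply; under purely simple allocation it would not be.

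**The case against.** The strongest reply is that the mismatch is one of wording. Sections 1.2 and 2.12 speak of improvement, which points to change scores. A t test on change is exactly the 2 × 2 interaction test, so power and analysis would agree and baseline would be used. A reader might infer from section 2.11 that baseline is discarded; the text does not establish that. It does place the baseline comparison only under the intragroup analysis, so the end-score reading is open too. What remains is that the variable is not stated, that change scores are less precise than ANCOVA, and that the Mann-Whitney alternative is not the interaction test.

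Covariates are often left to an analysis plan, and this is a condensed article. That stands: silence on covariates alone would not be a finding. Here the article itself names the tests, and they do not match its power basis. Leaving out centre contradicts nothing.

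A reader might also infer bias from chance baseline imbalance. Under randomisation the unadjusted test is unbiased, and its standard error already allows for such imbalance. Nor does Mann-Whitney rule out a non-inferiority estimate: it can be paired with a Hodges-Lehmann shift and interval.

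Lastly, the gain is not one number. It might be said that a correlation of 0.27 lifts ANCOVA to 80% at 40 per arm. That holds only if 0.61 is in final-score SDs. In change-score SDs the gain shrinks as ρ rises, and at 0.9 ANCOVA stays below 80%.

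**Conclusion.** The point holds as an inconsistency between sections 2.10 and 2.11, together with an avoidable loss of precision. On the end-score reading, the stated power is for another analysis, and the true power may be lower or higher: 55.1% at ρ = 0.7 and 89.0% at ρ = 0.3, against 76.9% for the interaction, when 0.61 is in change-score SDs. On the change-score reading, the parametric test is the interaction test, and ANCOVA's variance is 25% to 15% lower for ρ of 0.5 to 0.7. On both readings, leaving out pathology makes the test conservative if allocation is truly balanced on it; false positives do not increase.

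The size rests on an assumed correlation, an unstated effect-size scale and 40 per arm. That section 2.10 asks for 60 per group is a separate conflict, and at 60 the gain is smaller. The direction, in favour of ANCOVA, did not change in any case computed.

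**What to change.** In section 2.11, make the primary between-group analysis of WHODAS-12 and of MoCA an ANCOVA of the 12-week score on arm, baseline score and pathology. Centre may be added for precision. Report the adjusted difference with its 95% confidence interval, using robust or bootstrap standard errors if residuals are skewed. Keep the t test and Mann-Whitney test as sensitivity analyses, and state whether each is on end scores or change.

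Restate section 2.10 for that model, giving the scale of 0.61, the assumed pre-post correlation and its source, and what the 4 variables are.

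The cost is wording in the protocol and analysis plan plus one recalculation. The covariates are already collected.

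### The within-group before/after comparison names an unpaired t test for paired data; probably a slip, but wrong and inefficient if followed as written

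*Protocol article*

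**What the plan says.** Section 2.11 of the protocol article (Statistical analyses) chooses parametric or non-parametric tests according to the data distribution, and names two families.

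- **Between groups:** the independent Student t test or the Mann–Whitney U "test will be used to compare the 2 groups".
- **Within groups:** a Student t test or a rank test, set out in these words: "test for unpaired samples or the Wilcoxon signed-rank test will be used to compare the data collected at the first evaluation and the end". The sentence then labels this comparison in its closing words, "of the treatment (intragroup analysis").

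Other sections settle the data structure. Section 2.6 (Study population) says: "Clinical evaluations will be administered blindly, before and after the treatments". Section 2.10 (Sample size) assumes "an effect size of 0.61, 4 variables, and 2 repeated measurements". The significance level is fixed in 2.11: "Statistical significance will be set at bilateral alpha level of 0.05". No section names a paired t test.

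**The concern.** A first-versus-last comparison inside one arm uses two scores from each patient. An unpaired t test treats them as scores from two separate sets of people. It therefore ignores the correlation between a patient's two scores, and its standard error and p-value are wrong whenever that correlation is not zero.

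The sentence is also inconsistent within itself, because its non-parametric option, the signed-rank test, is paired. Read literally, a scale judged normally distributed would get a test that ignores the pairing, while a skewed scale would get one that uses it. Within-group p-values would then not be comparable across the many scales in section 2.7.

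At stake is the chance of detecting real change within an arm.

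**Working it through.** **No stated figure to reproduce.** The protocol gives no power or standard error for the within-group test.

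**Inputs**

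- Two-sided α = 0.05 (section 2.11).
- Patients per arm: 40, from section 2.2 ("we plan to enroll a total 40 stroke patients (20 for each treatment setting) and 40 TBI patients (20 for each condition"), so 20 + 20 = 40, reading the totals as covering both units. Section 2.10 instead says: "we calculated a minimal sample size of 60 participants per group in this study, given a power of >80"%. Both 40 and 60 are used below.
- Before/after correlation ρ: not given. Assumed 0.3, 0.5 and 0.7.
- True within-arm change: not given. Assumed 0.4 SD, with 0.61 SD as a sensitivity value.
- Equal SD before and after: assumed.

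**Step 1: standard errors, in SD units**

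Unpaired: √(2/n). Correct for paired data: √(2(1−ρ)/n). The ratio is 1/√(1−ρ), whatever n is.

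**Step 2: true size of the unpaired test** (large sample): 2 × [1 − Φ(1.96/√(1−ρ))].

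| ρ | SE ratio | 1.96 × ratio | True size |
|---|---|---|---|
| 0.3 | 1.20 | 2.34 | 1.9% |
| 0.5 | 1.41 | 2.77 | 0.6% |
| 0.7 | 1.83 | 3.58 | 0.03% |

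Simulation with n = 40 (40,000 runs) gave 0.68% unpaired against 4.8% paired at ρ = 0.5, and 0.06% against 5.3% at ρ = 0.7. The pattern is the same, with slightly higher unpaired values in the finite sample.

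**Step 3: power for a 0.4 SD change**

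The unpaired test rejects when the mean change exceeds its critical value times √(2/n), but the mean change actually varies with SE √(2(1−ρ)/n). For n = 40 and ρ = 0.5:

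- rejection threshold: 1.96 × 0.2236 = 0.438
- true SE: √(1/40) = 0.158
- power: 1 − Φ((0.438 − 0.4)/0.158) = 1 − Φ(0.24) = 0.40

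For the paired test, the noncentral t with n − 1 degrees of freedom and noncentrality 0.4/0.158 = 2.53 gives 0.69. The other rows follow in the same way.

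| n per arm | ρ | True SE | Unpaired, critical value 1.96 | Unpaired, t critical value | Paired |
|---|---|---|---|---|---|
| 40 | 0.5 | 0.158 | 40% | 39% | 69% |
| 40 | 0.7 | 0.122 | 38% | 36% | 89% |
| 60 | 0.5 | 0.129 | 63% | 62% | 86% |
| 60 | 0.7 | 0.100 | 66% | 65% | 98% |

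The t critical values are 1.991 (78 degrees of freedom) and 1.980 (118). The choice moves the unpaired power by one or two points, and simulated values (39%, 37%, 62%, 65%) lie within a point or so of both columns.

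**Step 4: sensitivity to a larger change**

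The only effect size in the protocol, 0.61, is stated for an interaction on an unclear metric. It serves here only as a larger trial value. Simulated power for a 0.61 SD change, unpaired against paired:

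- n = 40: about 85% against 96% (ρ = 0.5); about 90% against over 99% (ρ = 0.7)
- n = 60: about 97% against over 99% (ρ = 0.5); about 99% against over 99% (ρ = 0.7)

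**The case against.** The strongest reply is that this is a one-word slip. The independent t test has already been assigned to the between-group comparison. The questioned test is then set in contrast to it, coupled with a paired rank test, and labelled intragroup. An analyst would very likely run the paired test anyway. That explanation is probably right, and it lowers the weight of the point. It does not remove it, because this sentence is the operative analysis rule and nothing else in the protocol corrects it.

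Three stronger readings are tempting, and the document does not support them.

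- **A reader might infer that the trial's main conclusion is at risk.** Section 2.11 gives the between-group comparison its own tests, which this error does not touch. No section rests a superiority or noninferiority conclusion on a within-group test.
- **A reader might infer that the error could produce false claims of benefit.** With positive correlation the p-values are too large, so it cannot do so by this route. Only a negative before/after correlation would reverse the direction, which is implausible for repeated scores in the same patients.
- **A reader might infer that real changes will generally be missed.** That depends on the size of the change and on n, neither of which is fixed for this analysis. Step 4 shows a small loss for larger changes.

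It is also tempting to ask that within-group changes be declared descriptive and reported with confidence intervals. That is a separate matter of reporting, commonly left to an analysis plan, and it does not follow from this error.

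**Conclusion.** The point holds as an error of specification with limited reach: the parametric within-group test named is for independent samples, and the data are paired. The inflation of the standard error depends only on ρ, given equal SDs, and vanishes only at ρ = 0. The loss of power also depends on the assumed change and on which of the protocol's two sample sizes applies. For 0.4 SD it is roughly 30 points (ρ = 0.5) to 50 points (ρ = 0.7) with 40 per arm, and 24 to 33 points with 60. For 0.61 SD it is about 10 points with 40 per arm and 3 points or less with 60.

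Because the error is conservative, is probably a slip, and is confined to the parametric within-group analysis, it should be fixed but does not threaten the trial's main comparison.

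**What to change.** In section 2.11, change the parametric within-group test to the Student t test for **paired** samples and leave the Wilcoxon signed-rank test as its alternative. Nothing else in the sentence needs to change. With the paired test the size returns to 5% and the standard error uses the before/after correlation. The cost is one word, with no effect on data collection, sample size or the between-group analysis.

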### Background and rationale

1.1

Severe acquired brain injury (SABI) is damage to the brain, occurring after birth from traumatic or nontraumatic causes, and often resulting in deterioration of physical, cognitive, and emotional functions.^[1]^ SABI include a variety of acute brain lesions characterized by the occurrence of variably prolonged coma (24 hours), and simultaneous motor, sensory, cognitive, and/or behavioral impairment that causes a certain degree of disability. Congenital, perinatal, or degenerative-progressive brain injuries are excluded from this definition. The most common causes of SABI are traumatic brain injury (TBI), anoxic encephalopathy and ischemic or hemorrhagic stroke. These conditions mostly affect individuals from the fifth decade onwards and represent about 40% of the SABI. Further nontraumatic SABI arises from brain tumors, infections, and toxic-metabolic encephalopathy.^[2]^ Despite the fact that steady progress has been made toward prolonging patients’ survival and several pharmacologic and neuromodulating strategies have been proposed, results on functional recovery of SABI are still scarce.^[1,2]^

Functional recovery following SABI usually reaches its peak at around 6 months, and begins to decline as soon as 1 year after SABI, although rehabilitation may be effective also in the chronic phase. Thus, the increasing use of rehabilitation postdischarge may result in better motor and cognitive recovery. To this end, supervised stroke rehabilitation in the community for up to 1 year was associated with faster recovery and better functional status than with unsupervised therapy.^[1,2]^

Unfortunately, due to healthcare costs, patients are discharged before reaching the desired autonomy.

Providing rehabilitation at home is limited by high costs and rehabilitation provider availability. Thus, the use of home-based, exercise-oriented interventions by means of TR may be decisive. Indeed, TR allows for continuity of service through the entire rehabilitation cycle including assessment, intervention, consultation, and education, and it has recently emerged as an effective tool to provide rehabilitation care to patients early discharged at home, increasing clinical outcomes, by affording early reintegration and positively enhancing QoL.

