### Expected outcomes

2.12

1.Patients undergoing TR training will have a greater (or at least the same) improvement in nearly all the motor and cognitive scale scoring administered, with reduced disability (as evaluated by BI and WHODAS2).2.We expect that acceptability and feasibility measures will be significantly higher in the TR group when compared with the conventional treatment, with a concomitant decrease of the caregiver's burden (as per CBI and BDI).3.From the economic point of view, we expect that TR may be a sustainable, low-cost and effective way to deliver rehabilitative interventions.

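### The only test expressly assigned to change over time is within each arm; the between-arm test names no quantity, although the sample size is built on an interaction

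*Protocol article*

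**What the plan says.** The aims are comparative. Objectives asks whether improvement under TR is greater than, or at least equal to, that under traditional in-home rehabilitation. Trial design adds a non-inferiority aim. Expected outcomes predicts that "Patients undergoing TR training will have a greater (or at least the same) improvement in nearly all the motor and cognitive scale scoring administered".

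Statistical analyses offers two kinds of test in one sentence:

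- Between arms: "the independent Student *t* test or the Mann–Whitney *U* test will be used to compare the 2 groups". Whether this means end scores or changes is not stated.
- Within arms: the Wilcoxon signed-rank test or a t test, which "will be used to compare the data collected at the first evaluation and the end of the treatment (intragroup analysis").

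One threshold covers both: "Statistical significance will be set at bilateral alpha level of 0.05". Neither test is ranked above the other, and neither is linked to the first expected outcome.

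Sample size gives a different target. It asks for at least 60 patients in each arm, and its power statement reads: "given a power of >80% to detect an interaction in the 2-way repeated measures". The other inputs listed there are an effect size (0.61), the number of variables (4) and the number of measurement occasions (2).

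On the natural course, Background and rationale states: "Functional recovery following SABI usually reaches its peak at around 6 months". Eligibility criteria admits patients with a "diagnosis of stroke and TBI (less than 1 year"). Under Study population, both arms receive about one hour of treatment a day, 5 days a week, for 12 weeks.

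**The concern.** The null hypothesis of an intragroup test is that the arm did not change over 12 weeks. Spontaneous recovery, active treatment and practice on the scales can each make that null false in both arms, whether TR is better than, equal to or worse than UTRT. Randomisation protects against this only if the arms are compared with each other.

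Because the word for change is attached only to the intragroup test, a report that follows the text could set two within-arm p-values side by side. Significant in TR but not in UTRT would then look like greater improvement, and significant in both would look like the same improvement. Neither pattern tests the difference between arms. At stake is whether the first expected outcome is answered by the randomised comparison or by two uncontrolled before-after comparisons.

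**Working it through.** **1. The plan's own figure.** The basis for 60 per group is an interaction with effect size 0.61; metric, correlation and any alpha split are not given. For two means, n per group = 2[(z_alpha + z_power)/0.61]².

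- Two-sided 0.05: 42.2, so 43 at 80% power; 56.5, so 57 at 90%.
- Two-sided 0.05/4 = 0.0125 (one share per variable): 59.9, so 60 at 80%.
- Difference in change of 0.61 baseline SD, pre-post correlation 0.3 (variance of change 2 × 0.7 = 1.4): 59.1, so 60 at two-sided 0.05 and 80%.

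So 60 can be reproduced as a between-arm comparison, but only on inferred readings. No reading makes an interaction out of a within-arm test.

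**2. Inputs for the within-arm check.**

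- From the article: 40 per arm (Eligibility criteria: 20 stroke and 20 TBI patients per setting) and two-sided 0.05.
- Assumed, because the article gives neither: a gain g of 0.2 to 0.5 SD common to both arms, and a pre-post correlation ρ of 0.5 to 0.7. Scores are taken as normal with SD 1.

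**3. Formula.** The SD of change is √[2(1 − ρ)]: 1.000 at ρ = 0.5 and 0.775 at ρ = 0.7. The paired t test has noncentrality g√n/√[2(1 − ρ)] on n − 1 df. If p is its rejection probability and the arms are equal and independent, exactly one arm is significant with probability 2p(1 − p).

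**4. Results, 40 per arm, no TR-UTRT difference.**

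| ρ | gain (SD) | noncentrality | TR significant | exactly one arm significant |
|---|---|---|---|---|
| 0.5 | 0.2 | 1.26 | 24% | 36% |
| 0.5 | 0.3 | 1.90 | 46% | 50% |
| 0.5 | 0.5 | 3.16 | 87% | 23% |
| 0.7 | 0.2 | 1.63 | 36% | 46% |
| 0.7 | 0.3 | 2.45 | 67% | 44% |
| 0.7 | 0.5 | 4.08 | 98% | 4% |

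Simulation with 20,000 trials per scenario agrees within about one percentage point. In the simulations the between-arm t test rejected in about 5% of trials at every gain, on change or on end score. At 60 per arm and ρ = 0.5, TR is significant in 33%, 63% and 97% for gains of 0.2, 0.3 and 0.5 SD.

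**5. If TR is worse.** Let UTRT gain 0.8 SD and TR 0.5 SD; 0.8 lies outside the range above and is only an illustration. Both arms are significant in 0.869 × 0.999 = 87% of trials at ρ = 0.5 and 98% at ρ = 0.7. The between-arm test of change has noncentrality 0.3√20/√[2(1 − ρ)] = 1.34 or 1.73, so it detects the deficit in only 26% or 40%. Two significant within-arm tests beside a non-significant between-arm test would therefore be common although TR is worse. Only the confidence interval for the arm difference shows how much worse it could be.

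**6. The wording of the t test.** The article calls the intragroup t test one for unpaired samples. That is a separate error. Taken literally, at ρ = 0.5 and 40 per arm, TR is significant in 7%, 19% and 64% of trials for the same three gains. The pairing changes the rates; the hypothesis tested stays the same.

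**The case against.** A reader might infer that the intragroup test is the only planned test of improvement. The documents do not support that. The first half of the same sentence plans a comparison of the two groups. Under randomisation, a comparison of end scores or of changes estimates the TR-UTRT effect and keeps its error rate at about 5%. This stands, and the point is narrowed to it.

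A reader might also set the 24% to 98% against a nominal 5% and call it an inflated error rate. It is not. If patients recover, the within-arm null is false and rejecting it is correct. The percentages show only that such a rejection says little about TR against UTRT.

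Nor does any section say that success will be judged on within-arm p-values. Expected outcomes lists expectations, not decision rules, so the misreadings are a risk and not a stated plan. The recovery premise also has limits: Background and rationale says function can begin to decline as early as 1 year after injury, so some patients may be past their peak.

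Finally, the choice between end score and change is often left to an analysis plan, and this is a condensed article. That would excuse silence. Here the article does assign tests: it attaches change over time to the within-arm test, gives it the same alpha as the between-arm test, and lists nothing that matches the interaction on which it sized the trial. That mismatch is within the document.

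**Conclusion.** The point holds in a limited form. The plan has a valid between-arm test but does not say what it compares. It ties change over time only to within-arm tests, which cannot support a claim of greater or equal improvement, and its listed tests do not match the interaction in Sample size. With equal arms and 40 per arm, the TR within-arm test would be significant in about 24% to 98% of trials and exactly one arm in about 4% to 50%, against about 5% for a between-arm test. These figures rest on normal scores, a correctly paired test, and the assumed gains and correlations. The direction needs only some common gain in both arms. This is a weakness of specification that is easily corrected; it does not show that the trial will draw a wrong conclusion.

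**What to change.** In Statistical analyses, for each primary outcome (WHODAS-12 and MoCA):

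1. Name the between-arm difference in end-of-treatment score adjusted for baseline, with its 95% CI, as the analysis. The between-arm difference in change is the alternative; with two measurements it is the group-by-time interaction. Baseline adjustment is at least as precise: the per-patient variances for end score, change and adjusted score are 1, 2(1 − ρ) and 1 − ρ², that is 1, 1 and 0.75 at ρ = 0.5, and 1, 0.6 and 0.51 at ρ = 0.7.
2. State in Sample size that the interaction is group by time, so that the two sections agree.
3. Report within-arm change descriptively, as mean change with 95% CI and no p-value.
4. State that no claim of superiority or of the same improvement rests on intragroup tests, and tie the first item of Expected outcomes to the between-arm estimate.

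The cost is wording in three sections. Both measurements are already planned, so no patients or visits are added. The trial gives up within-arm p-values, which would probably have looked favourable.
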